### Protocol Development

#### Delivery Program

The intervention is delivered via a mobile phone using a WeChat miniprogram called OkeyMind. OkeyMind was initially tested during the COVID-19 pandemic in 2020. A pilot program was deployed to assess mental health conditions and promote mental health literacy among college students (n=254). Positive feedback from both students and staff emphasized the program’s usability, accessibility, and relevance. Insights from this pilot informed the development of OkeyMind, improving its user interface, engagement strategies, and intervention content, with a focus on social anxiety, while maintaining high completion and satisfaction rates.

OkeyMind differentiates itself from other mobile mental health interventions through 3 main features [30]: (1) targeted focus on social phobia, (2) innovative content delivery methods, and (3) integration of evidence-based mindfulness. OkeyMind is specifically designed to address social phobia, providing tailored psychoeducation and interventions that directly target social anxiety symptoms. To enhance engagement, OkeyMind uses cartoon-based video clips, influencer interviews, real-life cases from internet celebrities, and engaging animations, making psychoeducation more interactive and appealing to youth. This approach helps maintain attention and improves information retention compared with traditional lecture-style content. OkeyMind incorporates mindfulness practices developed by the Jockey Club “Peace and Awareness” Mindfulness Culture in Schools Initiative, which have been empirically shown to reduce stress, regulate emotions, and enhance overall well-being [31]. This evidence-based component strengthens the intervention’s effectiveness at supporting mental health.

OkeyMind features 3 main modules: self-learning module, psychological assessment tools, and meditation demonstrations. Participants can simply search “OkeyMind” on the WeChat miniprogram platform and access it free of charge. The mobile psychoeducation program (OkeyMind), based on the WeChat miniprogram, includes both psychoeducation and meditation components. Participants will complete the components as well as the psychological assessment tools at their own pace. For meditation practices, a tutorial video will be provided for guidance. All content is fully automated. No co-intervention will be provided alongside OkeyMind. To prevent delays in the intervention or follow-up assessments, an automated reminder function was developed. This feature ensures that participants receive pop-up reminders via WeChat if any delays occur. Trained research assistants will remind participants to engage in the activities (eg, intervention sessions, assessments) according to the study timeline and will be available to answer questions via social media platforms (eg, WeChat), phone calls, or messages.

#### Intervention Group—OkeyMind

This system features 3 main modules: self-learning modules, psychological assessment tools, and meditation demonstrations.

#### Self-Learning Modules

To design an appealing psychoeducation component for young adults, self-learning modules feature cartoon-based video clips, interviews with popular influencers, real-life cases from internet celebrities, and engaging animations. These entertaining and lively formats provide insights into social anxiety, educating users on the condition’s characteristics, coping mechanisms, and guidance for seeking professional assistance. By rejecting dull content and incorporating elements that resonate with youth, these resources aim to effectively educate and support young adults.

#### Psychological Assessment Tools

The program incorporates interactive, user-friendly tools designed to evaluate and monitor the youth using the program. These tools might include questionnaires and scales that assess levels of social anxiety, depression, and other relevant psychological states. Tailored to provide immediate feedback, the assessments are structured to be engaging, ensuring users are motivated to complete them. By analyzing responses, the program can offer personalized insights and track progress over time, allowing users to understand their mental health patterns better. This feature aids with not only self-awareness but also identifying areas where intervention might be needed, enhancing the overall effectiveness of the psychoeducation provided.

#### Meditation Demonstration

The program features guided meditation sessions led by calming, animated figures designed to appeal to young adults. These sessions aim to introduce users to various meditation techniques that can help manage symptoms of social anxiety. Each demonstration focuses on a specific meditation practice, such as mindfulness or breathing exercises, offering step-by-step guidance in a visually engaging and easy-to-follow manner. Through these demonstrations, users can learn and practice meditation in a way that is both informative and soothing, fostering skills that contribute to emotional and mental well-being.

Additionally, OkeyMind incorporates several strategies to improve adherence to intervention protocols and implements procedures for monitoring compliance, including (1) progress tracking, (2) reminders and notifications, and (3) optimal content length. Progress tracking includes features to monitor users’ progress over time, such as module completion. This functionality not only encourage continued engagement but also helps users see tangible signs of their journey and growth. The reminders and notifications use automated prompts to encourage consistent use of the app’s features and adherence to prescribed self-help activities. These reminders can play a critical role in fostering a routine and ensuring the beneficial use of the app. To ensure optimal content length, each video clip should be around 3 minutes to 5 minutes long, concise enough to maintain attention while providing substantial information or insights. Furthermore, complex concepts are broken down into digestible parts, with each video focusing on a single topic or coping strategy. This modular approach allows users to progress at their own pace.

#### Control Group—Waiting List

Participants in the waiting list control group will have access to the OkeyMind intervention withheld until after the 3-month follow-up assessment. To prevent confounding effects from relevant concomitant care and interventions, participants will be required to refrain from receiving any other treatments or interventions specifically targeting social phobia during the study period.

### Outcomes

Basic demographic and clinical data, including age, gender, region, and socioeconomic status, will be collected. The primary outcome will be social anxiety symptoms, assessed using SPIN. Secondary outcomes include depressive symptoms, measured using the Patient Health Questionnaire-9 (PHQ-9), and quality of life, evaluated using the EQ-5D-5L, which will also be used for cost analysis. All outcomes will be self-assessed using online measurements at baseline, postintervention, and the 3-month follow-up (Figure 2).

**Figure 2 figure2:**
[figure not shown]
SPIRIT (Standard Protocol Items: Recommendations for Interventional Trials) checklist. PHQ-9: Patient Health Questionnaire-9; SPIN: Social Phobia Inventory.

The primary outcome is social anxiety symptoms measured using SPIN. Developed by Antony et al in 2006 [32], SPIN is a brief self-report tool consisting of 17 items that assess fear, avoidance, and physiological discomfort in social situations. It is specifically designed for use with social anxiety disorder [32]. The Chinese version of the SPIN has been examined with good internal consistency (Cronbach α=0.85) and test-retest reliability (r=0.73). A cutoff value of 25 or higher has demonstrated strong reliability and validity and is commonly used to screen for social anxiety in the Chinese population [33].

Secondary outcomes include depressive symptoms measured using the PHQ-9 and quality of life measured using the EQ-5D-5L. The PHQ-9 is widely used to screen for the presence and severity of depression, monitor the severity of depression over time, and assist with the diagnosis of depression. Each of the 9 items is scored from 0 (not at all) to 3 (nearly every day), with a total score ranging from 0 to 27. Higher scores indicate more severe depressive symptoms. PHQ-9 scores of 5, 10, 15, and 20 represent mild, moderate, moderately severe, and severe depression, respectively. The Chinese version of the PHQ-9 demonstrates high internal validity and consistency, evidenced by a Cronbach α of 0.86 and strong test-retest reliability with a correlation coefficient of 0.86, affirming its efficacy for use in Chinese-speaking populations [34].

EQ-5D-5L is an established tool for assessing the general health status of individuals across a wide array of health conditions and treatments [35]. It measures health outcomes in 5 dimensions: mobility, self-care, usual activities, pain and discomfort, and anxiety and depression. Each dimension is rated on a 5-level scale, from no problems (level 1) to extreme problems (level 5), facilitating a comprehensive evaluation of a patient’s health-related quality of life. The total score is derived by converting the individual dimension scores into a single summary index value, reflecting overall health status, with higher scores indicating better health outcomes. Research supports the EQ-5D-5L’s reliability and validity among Chinese-speaking populations, showing good internal consistency with a Cronbach α between 0.76 and 0.79 [36-38].

To assess participant adherence, usage metrics will be analyzed using log files. This includes the number of video views, instances of video interruptions, intervention completion dates, and assessment completion dates. Completion rates will be classified as follows: ≥81% indicates sufficient engagement, 61%-80% indicates moderate engagement, 41%-60% indicates partial engagement, and ≤40% indicates poor engagement. These engagement levels will be correlated with outcomes to assess intervention effectiveness. To evaluate external validity, a feedback scale will be used to collect qualitative data from participants. This scale will focus on how the intervention translates into their daily lives, covering aspects such as satisfaction with social functioning, academic or job performance, and other relevant real-world outcomes.

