### Analysis

#### Effectiveness Analyses

The primary hypothesis for the between-group difference in the primary outcome will be tested using a linear mixed-effects model. This model accounts for responses at postintervention and the 3-month follow-up, incorporating baseline outcome measures and intervention assignment as fixed effects, with a participant-specific random intercept. An interaction between time and the randomized group will also be fitted as a fixed effect to allow estimation of treatment effect at all time points. A similar approach will be used for the secondary outcome analysis. The imputation of missing values will be based on the assumption that data are missing at random. The primary analyses will follow the intention-to-treat principle, meaning participants will be analyzed based on their originally assigned groups, regardless of their adherence to entry criteria, the treatment received, or any withdrawal or deviation from the protocol [39]. The data will be automatically generated by the WeChat miniprogram once participants complete the process, eliminating the need for manual data entry. A *P* value <.05 will be used as the level of statistical significance. Data analysis will involve at least 2 statisticians or researchers and will be processed and verified using various statistical software, such as SAS and SPSS.

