### Limitations

Given that all intervention sessions and evaluations are conducted online and the research period extended over several months, there is potential for a relatively high attrition rate compared with on-site interventions. To address this issue, several measures are implemented. First, during the screening stage, interviews are scheduled to ensure each participant has the proper motivation and desire to participate, helping to select committed individuals more likely to complete the program. Second, support is provided during interventions and assessments, with manpower allocated to address any issues. Reminder systems, such as texts or calls, are implemented to prompt participants when delays occur, aiming to keep them engaged and on track. Third, the technology and software team continuously improves the user experience based on participant feedback, enhancing video quality and reducing buffering times to ensure a smoother and more enjoyable experience, thus reducing dropout rates due to technical frustrations.

Additionally, the technological nature of OkeyMind may limit the program’s generalizability. Youths familiar with using social media and WeChat miniprograms are likely to benefit more from the intervention than older adults who may be less familiar and comfortable with these digital platforms. This discrepancy in technological proficiency could impact the overall effectiveness and reach of the program across different age groups, potentially introducing bias in the results and affecting the external validity of the study. Future research should consider addressing this limitation by exploring ways to make the program more accessible and user-friendly for older adults.

Last, achieving complete participant blinding could be challenging, particularly in behavioral interventions such as this study. Participants could infer their group assignment, introducing potential performance and self-report biases. However, using a waiting list rather than a no-treatment control ensured that control participants still anticipated full access to the intervention after follow-up, potentially softening, though not eliminating, these biases. Future studies should adopt more rigorous designs, such as concurrently running 2 active intervention arms, to mitigate performance and self-report biases.

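### Correlating engagement with outcomes inside the OkeyMind arm cannot assess effectiveness; the sentence should make it descriptive or exploratory

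*Protocol article*

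**What the plan says.** In Methods, Outcomes, the article introduces the usage data with an adherence purpose: "To assess participant adherence, usage metrics will be analyzed using log files". It then sets the bands: "Completion rates will be classified as follows: ≥81% indicates sufficient engagement, 61%-80% indicates moderate engagement, 41%-60% indicates partial engagement, and ≤40% indicates poor engagement". The next sentence gives the use to which they will be put: "These engagement levels will be correlated with outcomes to assess intervention effectiveness".

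Two other sections determine what kind of variable engagement is. Delivery Program makes use self-paced: "Participants will complete the components as well as the psychological assessment tools at their own pace". Control Group—Waiting List says: "Participants in the waiting list control group will have access to the OkeyMind intervention withheld until after the 3-month follow-up assessment".

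The confirmatory test is described separately, under Effectiveness Analyses: "The primary hypothesis for the between-group difference in the primary outcome will be tested using a linear mixed-effects model". That analysis follows the intention-to-treat principle and does not use engagement.

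**The concern.** How much of the program a person completes is decided by that person after randomisation. Someone who is more motivated, less severely affected at baseline, or already improving may complete more and also report a lower SPIN score, whether or not the content works. The causal order can also run backwards, with change in symptoms driving use. Nothing in a correlation between completion band and outcome separates these routes from a true effect.

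During the comparison period the waiting list has, by assignment, no OkeyMind completion to correlate. The association is therefore in effect a one-arm observational result, and the randomised control contributes nothing to it.

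What is at stake is the label. The sentence gives effectiveness as the purpose, so a positive correlation would be reported as bearing on whether OkeyMind works. It could be positive with no effect at all.

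**Working it through.** The article attaches no figure to this correlation, so there is none to reproduce. The check asks how often the correlation would look favourable if OkeyMind did nothing.

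**Inputs from the article**
- 90 participants per arm and 10% anticipated attrition (Recruitment): 90 × 0.90 = 81 completers in the OkeyMind arm.
- Four ordered engagement levels (Outcomes).
- Significance level .05 (Effectiveness Analyses). Two-sided testing is assumed, because the article does not state sidedness.

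**Assumptions not in the article**
- The true effect of OkeyMind is zero.
- One unmeasured trait U (for example motivation) has correlation a with engagement E and the same a with improvement Y. The main range for a is 0.3 to 0.5.
- The four bands are equally filled.
- The correlation is tested for significance, which the article does not say.

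**Step 1: expected correlation, engagement kept continuous.** With E = aU + √(1−a²)·e₁ and Y = aU + √(1−a²)·e₂, where e₁ and e₂ are independent, corr(E, Y) = a². For a = 0.3, 0.4 and 0.5 this gives 0.09, 0.16 and 0.25, all spurious.

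**Step 2: chance of significance, engagement kept continuous.** By the Fisher transformation, the test statistic has mean atanh(a²)·√(n−3) and unit variance, with √78 = 8.83.
- a = 0.3: 0.0902 × 8.83 = 0.80, giving 12.5% two-sided.
- a = 0.4: 0.1614 × 8.83 = 1.43, giving 29.7%.
- a = 0.5: 0.2554 × 8.83 = 2.26, giving 61.6%.

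**Step 3: the planned four bands.** Engagement was cut into four levels and tested with a Spearman correlation in 5,000 simulated trials per setting. Only significant results in the favourable direction were counted, for which the nominal rate is 2.5%.

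| a | Mean rho, n = 81 | Favourable and significant, n = 81 | Favourable and significant, n = 90 |
|---|---|---|---|
| 0 | 0.00 | 2.4% | 2.6% |
| 0.3 | 0.08 | 10.8% | 10.3% |
| 0.4 | 0.14 | 25.5% | 27.0% |
| 0.5 | 0.23 | 52.8% | 58.3% |
| 0.6 | 0.33 | 85.9% | 89.4% |

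The banded figures are lower than those in step 2, mainly because banding weakens the correlation. They are the ones that match the planned analysis.

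**Step 4: comparator.** A randomised two-group t test with no effect and 81 per arm rejected in 4.8% of 5,000 runs (two-sided), which is its nominal level. The randomised comparison does not share the problem.

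**The case against.** The best defence is that this is a supplementary adherence analysis. The paragraph opens with adherence, the hypotheses are stated as OkeyMind against control, and the section on effectiveness assigns the primary hypothesis to a randomised mixed model. That stands. A reader might infer that the correlation is the trial's test of effectiveness, or that it could be used to rescue a null intention-to-treat result. The article supports neither reading: no hypothesis or decision rule rests on the correlation, and nothing lets it replace the primary result.

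A second defence is that an article may leave labels and covariate adjustment to a fuller analysis plan. That also stands for detail. It does not cover the purpose that the sentence itself states.

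Third, the size is illustrative. The trait correlations have no anchor in the article, and the bias could run the other way: if more distressed users engage more, a real effect would be masked. Limitations also says that "interviews are scheduled to ensure each participant has the proper motivation and desire to participate", which would narrow variation in motivation and so weaken confounding by it. Narrowing is not removal, however, and the same section presents committed people as more likely to complete, so the article itself links motivation to engagement.

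Finally, a reader might see holes in the bands, for example between 80% and 81% in "61%-80% indicates moderate engagement, 41%-60% indicates partial engagement". With completion rounded to whole percentages the bands are contiguous, so this is not part of the point.

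**Conclusion.** The point holds in a limited form. As worded, the article gives a self-selected, post-randomisation, within-arm association the purpose of assessing effectiveness, and such an association cannot do that. With zero true effect and an assumed shared trait correlation of 0.3 to 0.5, the banded correlation at n = 81 is favourable and significant in about 11% to 53% of trials, against 2.5% nominal. Those percentages depend on the assumed trait correlations, equally filled bands and a two-sided .05 test. The mechanism does not depend on any one of these values.

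The restriction to one arm is by assignment. Delivery Program says OkeyMind can be found on WeChat and used free of charge, so some use by waiting-list participants cannot be ruled out. The primary intention-to-treat analysis and its conclusion are untouched.

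**What to change.** **Wording.** Change the sentence in Outcomes to say that the association between engagement and outcomes will be reported as descriptive or exploratory, and that evidence of effectiveness rests on the randomised comparison under Effectiveness Analyses. The bands can stay as a description of use.

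**Optional analysis.** If an effect of engagement is wanted, add a supplementary instrumental-variable analysis (of the complier-average causal effect type), with randomised arm as instrument, percent completion as a continuous exposure, and adjustment for baseline SPIN. State two assumptions with it:
- Assignment affects SPIN only through use of the program. Expectancy could breach this, since Limitations accepts that participants may infer their group.
- The effect is roughly linear in completion.

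**Exposure to avoid.** Do not use the ≥81% level as a binary exposure, because benefit from partial use would bias the estimate. Take an assumed example with effect D at full completion, linear in completion, half the arm at 90% and half at 50%. The intention-to-treat effect is 0.5 × 0.90D + 0.5 × 0.50D = 0.70D. Dividing by the half who pass the cut gives 0.70D / 0.5 = 1.40D, against a true 0.90D in that half: 1.40 / 0.90 = 1.56, an overestimate of 56%. Dividing by mean completion instead gives 0.70D / 0.70 = D, as it should.

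**Cost.** One reworded sentence and, if the option is taken, one model on usage data already planned for collection. The downside of the option is a wider interval than the intention-to-treat one and the added assumptions.

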### Analysis

#### Effectiveness Analyses

The primary hypothesis for the between-group difference in the primary outcome will be tested using a linear mixed-effects model. This model accounts for responses at postintervention and the 3-month follow-up, incorporating baseline outcome measures and intervention assignment as fixed effects, with a participant-specific random intercept. An interaction between time and the randomized group will also be fitted as a fixed effect to allow estimation of treatment effect at all time points. A similar approach will be used for the secondary outcome analysis. The imputation of missing values will be based on the assumption that data are missing at random. The primary analyses will follow the intention-to-treat principle, meaning participants will be analyzed based on their originally assigned groups, regardless of their adherence to entry criteria, the treatment received, or any withdrawal or deviation from the protocol [39]. The data will be automatically generated by the WeChat miniprogram once participants complete the process, eliminating the need for manual data entry. A *P* value <.05 will be used as the level of statistical significance. Data analysis will involve at least 2 statisticians or researchers and will be processed and verified using various statistical software, such as SAS and SPSS.

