### Recruitment

The study will be conducted in school settings, including middle schools and tertiary institutions, across China. The trial aims to enroll 180 participants, with 90 assigned to each group [28]. This sample size accounts for an anticipated attrition rate of 10% and is expected to offer 90% statistical power. This determination is based on using an independent group *t* test, a significance level of .05, and an effect size of 0.35 (Cohen *d*), which falls within the small-to-medium range [29]. To recruit enough participants, school faculty help with recruitment, and digital flyers and promotional videos are shared through WeChat and school online platforms.

The participant inclusion criteria include (1) youths aged between 15 years and 24 years old who are (2) exhibiting mild or more severe social phobia (ie, Social Phobia Inventory [SPIN] score ≥25) and (3) have a smartphone with WeChat installed and basic internet literacy. The exclusion criteria include (1) being unable to attempt a baseline assessment (eg, due to being unpermitted to leave a psychiatric ward), (2) currently receiving another intensive psychological intervention, (3) currently holding an active suicidal plan, and (4) having a current diagnosis of psychological disorders (eg, schizophrenia, bipolar disorder). These data will be collected through self-report questionnaires, including questions such as: “Have you been previously diagnosed with any psychological disorders (eg, schizophrenia, bipolar disorder)? If yes, please specify.” Additionally, university tutors, who are familiar with students’ mental health conditions, will assist with identifying ineligible participants. Participants will be recruited and screened offline but will complete all interventions and assessments online. Participants are briefed through online tutorial video clips in the OkeyMind miniprogram; these clips demonstrate the research flow regarding intervention timing, follow-up frequency, and usage intensity.

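### Fitted as listed with default residuals, the random-intercept model assumes equal residual variance and one baseline slope at both visits, so visit-specific standard errors are wrong if the adjusted variances differ

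*Protocol article*

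**What the plan says.** The Effectiveness Analyses section of the protocol article describes one linear mixed-effects model for the primary outcome:

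- Data: "This model accounts for responses at postintervention and the 3-month follow-up".
- Fixed effects: "incorporating baseline outcome measures and intervention assignment as fixed effects".
- Random part: "with a participant-specific random intercept".
- Visit-specific effects: "An interaction between time and the randomized group will also be fitted as a fixed effect", with the stated purpose "to allow estimation of treatment effect at all time points".

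The secondary outcomes are to be handled in a similar way. No baseline-by-time term is listed. The residual structure is not stated, nor is any use of robust standard errors. No single visit is named as carrying the primary claim. The only SPIN correlation over time in the article is the test-retest value of 0.73 for the Chinese version (Outcomes section), without an interval. No SPIN standard deviation is given for any visit.

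**The concern.** The plan wants a treatment effect at each visit, and each needs its own correct standard error. With default residuals, a random intercept makes the total variance the same at both visits. With one baseline coefficient, it also cannot follow a baseline correlation that changes over time.

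After baseline adjustment with equal SDs, the residual variance is proportional to 1 − r². The program lasts 1 month and the last assessment is at 3 months, so a weaker correlation with baseline at the later visit is plausible. The model would then pool a smaller and a larger variance and apply the average to both contrasts. One contrast would be tested too liberally and the other too strictly. Since no visit is singled out, either contrast could be used to support the primary claim.

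**Working it through.** The article states no standard error, SD or visit variance, so it has no figure of its own to reproduce on this point.

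**Inputs.** From the article: 90 per arm with 10% attrition, so 90 × 0.9 = 81 per arm; significance level 0.05 (taken as two-sided); the two post-baseline visits; r = 0.73 as the one available SPIN correlation. Assumed: that 0.73 may stand for the baseline-to-postintervention correlation in most scenarios; all 3-month correlations; SDs relative to a baseline SD of 1.

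**Formulas.** Let r_j and s_j be the baseline correlation and the SD at visit j, and let β_j = r_j·s_j be the visit's own baseline slope. With complete data:

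- fitted common slope: b = (β₁ + β₂)/2
- residual variance at visit j around that slope: v_j = s_j² − 2·b·β_j + b²
- variance that the model uses at both visits: m = (v₁ + v₂)/2
- model SE divided by true SE at visit j: √(m/v_j)
- approximate type I error: 2·[1 − Φ(1.96·√(m/v_j))]

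**Worked case, 0.73 and 0.50, equal SDs.** b = (0.73 + 0.50)/2 = 0.615.

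- v₁ = 1 − 2(0.615)(0.73) + 0.615² = 0.480
- v₂ = 1 − 2(0.615)(0.50) + 0.615² = 0.763
- m = 0.622

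The SE ratios are √(0.622/0.480) = 1.138 postintervention and √(0.622/0.763) = 0.903 at 3 months. The approximate type I errors are 2.6% and 7.7%.

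**Scenarios.** The last column gives type I error from simulated null trials with 81 per arm (4,000 to 20,000 per scenario). A range means that separate runs differed.

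| r post / 3 months | SD post / 3 months | v₁, v₂ | SE ratio post / 3 months | Simulated type I error post / 3 months |
|---|---|---|---|---|
| 0.73 / 0.73 | 1 / 1 | 0.467, 0.467 | 1.00 / 1.00 | 4.8–5.0% / 4.5–5.0% |
| 0.73 / 0.65 | 1 / 1 | 0.469, 0.579 | 1.06 / 0.95 | 3.5% / 5.9% |
| 0.73 / 0.60 | 1 / 1 | 0.471, 0.644 | 1.09 / 0.93 | 3.1–3.6% / 6.5–6.9% |
| 0.73 / 0.50 | 1 / 1 | 0.480, 0.763 | 1.14 / 0.90 | 2.4–2.7% / 7.6–8.2% |
| 0.60 / 0.55 | 1 / 1 | 0.641, 0.698 | 1.02 / 0.98 | 4.1–4.6% / 5.5–5.6% |
| 0.60 / 0.60 | 1.2 / 1 | 0.925, 0.644 | 0.92 / 1.10 | 6.5% / 3.3% |
| 0.73 / 0.65 | 1.2 / 1 | 0.685, 0.590 | 0.97 / 1.04 | 5.4% / 4.1% |

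Where an unstructured 2 × 2 covariance with visit-specific baseline slopes was fitted to the same simulated data, type I error stayed at 4.4% to 5.5% at both visits, including the two reversed rows.

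**Power postintervention at d = 0.35.** With visit-specific variance and r = 0.73, SE = √(2 × 0.467/81) = 0.107 and power is Φ(0.35/0.107 − 1.96), about 90%. In the 0.73/0.50 case, the model SE is √(2 × 0.622/81) = 0.124 and the true SE is √(2 × 0.480/81) = 0.109. Power is then Φ((0.35 − 1.96 × 0.124)/0.109), about 84%. The 0.73/0.60 case gives about 87%.

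**Other tests from the same model.** Let c be the residual covariance between visits. The variance of the visit-averaged effect is proportional to (v₁ + v₂ + 2c)/4, and that of the group-by-time interaction to v₁ + v₂ − 2c. Replacing v₁ and v₂ by m leaves both unchanged, because v₁ + v₂ = 2m. Simulation agrees: in the 0.73/0.60 and 0.73/0.50 cases, type I error was 5.0% and 4.8% for the averaged effect, and 5.0% for the interaction in both.

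**The case against.** The strongest reply is that the article does not commit to equal variances. A random intercept can be combined with visit-specific residual variances or robust standard errors, and that detail is commonly left to an analysis plan, which is not shown here. The single baseline slope is likewise inferred from the listed terms. This stands: the point applies to the model as listed and fitted with default residuals, and it is wrong to say that a random intercept forces equal variances.

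A reader might also infer that the 3-month contrast is anticonservative as a matter of fact. The documents do not support that. They give no SD or baseline correlation by visit, the 0.73 is a retest value with no interval, and the 3-month correlations above have no source in the article. With equal adjusted variances there is no error, with a small decline it is slight, and with a larger postintervention SD it reverses.

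Nor does it follow that the primary test is inflated. The hypothesis concerns the between-group difference, and no single-visit contrast is named as primary. If the test is the averaged effect or the interaction, complete data leave it correctly calibrated.

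One possible defense does not remove the effect: that the SPIN entry cutoff of 25 restricts the baseline range. With baseline truncated at its mean or 1 SD above it, simulated 3-month type I error was still 6.5% to 6.7% (r = 0.60) and 7.5% (r = 0.50).

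**Conclusion.** The point holds conditionally and is modest in size. If baseline-adjusted variances differ between visits, the listed model with default residuals misstates the standard error of both visit-specific contrasts: too small where variance is larger, too large where it is smaller. Under the steeper declines in correlation considered (0.73 to 0.60 or 0.50, equal SDs, 81 per arm), the standard error is 7% to 10% too small at 3 months and 9% to 14% too large postintervention. Which visit is affected, and by how much, cannot be settled from the article. The plan is not shown to be in error; this is an improvement available at almost no cost, and it protects both contrasts whichever visit proves more variable.

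**What to change.** For the two post-baseline visits, replace the random intercept with an unstructured residual covariance. Fixed effects: group, visit, group-by-visit, baseline and baseline-by-visit. Estimate by REML with Kenward-Roger degrees of freedom. Apply the same model to PHQ-9 and EQ-5D-5L. Keep the random-intercept model only as a fallback for non-convergence.

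The cost is about one sentence in the Effectiveness Analyses section and two further parameters, one variance and one slope, which about 160 participants (2 × 81 = 162) can readily support. No additional data are needed.
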